**3 Sample size**

We utilized G*Power software (v3.1.9.2, University Dusseldorf, Germany; available for download from http://www.psychologie.hhu.de) to determine the sample size for our study. The primary outcome evaluation index considered in this study was FMA-UE. Prior to commencing the formal experiment, 15 patients who met the inclusion criteria were divided into groups in a 1:1:1 ratio. Sample size calculation was conducted for the main objective, which focused on the treatment effect 4 weeks after surgery. The results of the preliminary experiment revealed the following mean ± standard deviation values after 4 weeks of intervention: TCY+CRT treatment (35.5±9.5), RAT+CRT treatment (34.28±9.58), and CRT alone (29.00±10.2). Based on the G*power two-factor repeated measures analysis of variance (ANOVA) F test, a total sample size of 84 cases was determined for a two-tailed test with a power of 80% and a significance level of 5% (alpha error). Considering a 1:1:1 allocation ratio and accounting for a 10% dropout rate, we estimated that a final total of 93 patients (31 in each group) would be required.

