**Study design**

This study will be a single-center, three-arm, parallel-group, assessors-blind randomized controlled trial. All the patients will be informed of the study content before the subject recruitment. The patients who meet the inclusion criteria and agree to participate in the study will sign the informed consent. As shown in the study flow chart (**Fig.1**), the patients will be randomly allocated into 3 groups with equal sample size: 1) CRT group; 2) CRT+RAT group; 3) CRT+ BWS-TCY group. The rehabilitation interventions will last 4 weeks. Patients’ upper-limb functions will be assessed using rating scales before and after the interventions.

[figure not shown]

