**7 Outcome measures**

**7.1 Fugl-Meyer motor assessment- upper extremity**

The Fugl-Meyer motor assessment- upper extremity (FMA-UE) is the main index used in this study to measure upper limb motor dysfunction after stroke. It is a cost-effective clinical examination method that is widely used in stroke patients due to its reasonable design, simplicity, and ease of use^[45]^. The FMA-UE assesses reflex activities, shoulder, elbow, and wrist joint movement, as well as coordination. It consists of 8 aspects and 33 items, with each item scored on a scale of 0 to 2 points. The total score ranges from 0 to 66 points.

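### Section 3 does not support its stated 80% power with 84 patients: two pilot means do not fit five patients per arm, and 84 depends on unstated settings

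*Protocol*

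**What the plan says.** Section 3 (Sample size) of the protocol sizes the trial on FMA-UE: "The primary outcome evaluation index considered in this study was FMA-UE". The planning values come from a pilot in which "15 patients who met the inclusion criteria were divided into groups in a 1:1:1 ratio". They are reported as "mean ± standard deviation values after 4 weeks of intervention" and read "TCY+CRT treatment (35.5±9.5), RAT+CRT treatment (34.28±9.58), and CRT alone (29.00±10.2". No baseline pilot values are given.

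The calculation is described as "Based on the G*power two-factor repeated measures analysis of variance (ANOVA) F test", and the result is that "a total sample size of 84 cases was determined for a two-tailed test with a power of 80% and a significance level of 5" per cent. The section does not give the effect size f, the number of repeated measurements or the correlation between them. It also does not say whether the between-groups test or the interaction was sized.

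Three other places bear on this. Section 7.1 defines the scale: "It consists of 8 aspects and 33 items, with each item scored on a scale of 0 to 2 points", with a total of 0 to 66. Study design says that "upper-limb functions will be assessed using rating scales before and after the interventions". Section 4 places randomisation after baseline testing.

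**The concern.** There are two separate problems.

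The first is in the inputs. The three pilot means are the only effect information behind the sample size. A sum of items scored 0, 1 or 2 is a whole number, which limits the means that five patients can produce. Two of the three reported means fall outside that limit.

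The second is in the output. The means describe one time point, 4 weeks, but they were entered into a repeated-measures procedure. In such a procedure the result depends heavily on which effect is tested and on the correlation between visits, and neither is stated. In a trial randomised after baseline testing the expected baseline difference is zero. A test of the group mean averaged over baseline and 4 weeks therefore dilutes the effect.

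At stake is how a null result is read. It would be taken to come from a trial with 80% power, and section 3 as written does not establish that.

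**Working it through.** **Inputs.** Means 35.5, 34.28 and 29.00 and SDs 9.5, 9.58 and 10.2 (section 3); N = 84, alpha 0.05 (section 3); two visits, m = 2 (Study design). The correlation rho between visits is not in the protocol, so a range is shown. Power is taken from the noncentral F distribution with noncentrality λ. The degrees of freedom are 2 and N − 3 (N − 4 for the baseline-adjusted analysis).

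**Step 1: are the pilot means possible?** 15 patients split 1:1:1 is 5 per arm. A mean of five whole numbers is a multiple of 0.2.
- 5 × 29.00 = 145: possible.
- 5 × 35.5 = 177.5: not possible. It would be possible with 4 patients (142/4).
- 5 × 34.28 = 171.4: not possible. With ordinary rounding the smallest group that can give 34.28 is 18 (617/18 = 34.278). With truncation it is 7 (240/7 = 34.2857). Both exceed the 5 in the arm.

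**Step 2: effect size from the means as printed.**
- Grand mean = (35.5 + 34.28 + 29.00)/3 = 32.93.
- SD of the three means (divisor 3) = 2.821.
- Pooled SD = √[(9.5² + 9.58² + 10.2²)/3] = 9.765.
- f = 2.821/9.765 = 0.289, so f² = 0.0835.

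**Step 3: reproduce 84.** For the G*Power repeated-measures between-factors test, λ = f²·N·m/[1 + (m − 1)rho].
- f rounded up to 0.30, m = 2, rho = 0.5: λ = 0.09 × 84 × 2/1.5 = 10.08, power 80.3%. The next smaller equal allocation, N = 81, gives 78.7%. So 84 is the answer.
- f = 0.289, m = 2, rho = 0.40: λ = 10.01, power 80.1% at N = 84.
- f = 0.289, m = 2, rho = 0.5: power 77% at N = 84; 90 are needed.

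The G*Power within-between interaction option with f = 0.289, m = 2 and rho = 0.5 returns 33, not 84.

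**Step 4: comparison of the 4-week scores alone.** λ = N·f² = 84 × 0.0835 = 7.01, power 64%. 80% needs 120.

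**Step 5: equal baselines, two visits, full difference at 4 weeks only, N = 84.**
- Group main effect: averaging a zero and a full difference halves the effect, so λ = N(f/2)²·2/(1 + rho).
- Group-by-time interaction: λ = N·f²/[2(1 − rho)].
- Baseline-adjusted ANCOVA: λ = N·f²/(1 − rho²).

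| rho | Group main effect | Group × time | ANCOVA |
|---|---|---|---|
| 0 | 36% | 36% | 64% |
| 0.3 | 28% | 49% | 68% |
| 0.5 | 25% | 64% | 77% |
| 0.6 | 24% | 74% | 84% |
| 0.7 | 22% | 86% | 91% |
| 0.9 | 20% | >99% | >99% |

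The interaction reaches 80% from rho of about 0.65, and ANCOVA from about 0.55.

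**Step 6: simulation** (28 per arm, rho 0.5, f = 0.289). With the difference also present at baseline, the group test has 78% power and the interaction 5%. With equal baselines, the group test has 25% and the interaction 63%.

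**The case against.** The strongest reply is that nothing here proves the trial underpowered. A reader might infer that 84 patients cannot give 80% power, or that 80% requires a group difference at baseline. The protocol does not support either inference. With equal baselines, 84 gives 80% for group by time if rho is about 0.65 or more, and for a baseline-adjusted analysis if rho is about 0.55 or more. The protocol states no correlation, so such values are not excluded. This stands.

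It is also fair that the settings behind 84 are inferred. With f = 0.289, the between-factors test also returns 84 for three visits at rho of about 0.55 and for four at about 0.60. The visit count is itself unsettled: the protocol gives the intervention as both 4 and 12 weeks, passages that must be reconciled, and adds 12 weeks of follow-up. If the full difference held at every visit after baseline, the effect would be cut to 2/3 or 3/4 instead of 1/2. The group main effect would then have 46% or 59% power at rho 0.5. The 20-36% range therefore belongs to two visits only, although the power stays well below 80% in these variants.

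The figure of 120 is a benchmark for a different test, not a corrected value of the stated calculation.

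On the pilot, a slip in the reported arm sizes is possible. A reader might infer that the effect was not taken from the pilot at all, but the protocol does not show that. What it does show is that the stated means and the stated split cannot both be right.

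**Conclusion.** The point holds in this form: section 3 does not support its claim of 80% power with 84 patients.

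The conflict in the inputs needs no assumption about the test. It rests on five complete FMA-UE totals per arm and on the whole-number scoring in section 7.1. Missing pilot patients could explain 35.5 but not 34.28.

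The conclusion on the output is conditional. It takes the printed means and SDs at face value, a common SD at both visits, two visits and no expected baseline difference. On that basis, the test that returns 84 has about a quarter of the power claims' worth of certainty at rho 0.5 (25%, against the stated 80%). The two analyses suited to the design reach 80% only above a correlation that the protocol does not give. The stated power is therefore unsupported, which is not the same as shown to be unattainable.

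**What to change.** 1. Check the pilot data and correct the means or the number per arm in section 3.
2. Name the effect on which the trial is sized: group by time or, better, the 4-week score adjusted for baseline. It should not be the group main effect averaged over baseline.
3. State f, the number of visits and rho, with the source of rho.
4. Keep 93 patients and restate the power from the corrected inputs over a range of rho. The percentages above show the likely size of the change on the current means. They are illustrative until the pilot data are checked and should not be copied into the protocol.

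The cost is a check of 15 pilot records and the rewording of one section, with no extra patients. The downside is that the stated power may become less favourable.

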**4 Randomized grouping and allocation concealment**

In this study, a total of 93 subjects will be evenly divided into 3 groups, with 31 cases in each group. The groups will be named as follows: BWS-TCY group, CRT group, and RAT group. Subject randomization will be performed by an external professional statistician. After baseline testing, each participant received an envelope containing a randomly assigned serial number to determine their group. The random sequence will be generated by an independent professional statistician using SPSS software (IBM Corp., IBM SPSS Statistics, V25, Armonk, NY, USA), with the random number seed set to 20210608. Throughout this process, the statisticians, outcome assessors, and data analysts will be blinded to the study's recruitment, intervention, and evaluation. The randomization assignments ill be placed in sealed opaque envelopes by an independent researcher who will be also blinded to the trial. The identity of each participant is represented by a serial number, which is numbered according to their entry into the group. The letters 'A', 'B', and 'C' are used to represent the assigned groups, with 'A' corresponding to the BWS-TCY group, 'B' to the CRT group, and 'C' to the RAT group. The randomization process will be conducted by an independent researcher. Three rehabilitation therapists will be responsible for recruiting and assigning participants to conduct the intervention. Due to significant differences between the groups, neither the researchers nor the therapists will be blinded. The study will be designated as open-label, so the patients will be not blinded.

**5 Upper limb rehabilitation robot equipment and BWS-TCY program design**

The upper limb rehabilitation robot will use for BWS-TCY training and RAT training is Fourier Intelligence Co., Ltd.'s product called Fourier Arm Motus EMU. It will be a three-dimensional upper limb rehabilitation robot that operates on terminal control. The robot offers real-time, dynamic compensation for gravity and includes various games for upper limb training. These games involve activities like stretching the affected side's upper limb to musical notes in different directions (referred to as the 'grabbing the musical notes' game), simulating fishing actions and putting fish into boxes of different colors (known as the 'fishing game'), online imitation of table tennis with teammates (known as the 'table tennis game'), and activity training for various joints of the upper limbs.

BWS-TCY training utilizes the EMU robot's robotic arm to guide the affected upper limb in completing TCY movements. To facilitate this, a modified set of procedures was developed. The program consists of two modules: the first module focuses on generating customized TCY motion trajectories based on the specific characteristics of each patient, which are then saved for future training sessions. The second module is the training module, where the saved TCY trajectory can be selected and different modes (passive, assisted, and resistance) can be chosen based on the severity of upper limb impairment. The system also offers adjustable gravity compensation, as well as customizable time and range of motion. During training, the system computer simultaneously plays TCY action videos and soothing music.

**6 Interventions**

All patients will receive rehabilitation intervention in addition to routine medical treatment and daily care in the hospital. The patient's safety status will be continuously recorded throughout the intervention. The rehabilitation intervention will last for 12 weeks, with sessions of 60 minutes per day, 5 days per week.

**6.1 Intervention plan for CRT group**

In the CRT group, patients will receive 60 minutes of CRT treatment every day, will divide into two 30-minute sessions in the morning and afternoon. The training primarily focuses on the affected side and involves physical therapy, occupational therapy, and rehabilitation care. The training program includes various activities such as passive joint exercises, weight training with the assistance of the healthy hand, anti-spasm model training, functional activity series training for shoulder, elbow, and wrist joints, finger function and fine movement rehabilitation training, proper limb positioning, daily living ability training, turning over in bed training, balance training, and therapies such as proprioceptive neuromuscular stimulation technology therapy and Rood therapy.

**6.2 Intervention plan for RAT+CRT group**

After 30 minutes of CRT, the RAT training session began. The patient is seated in front of a computer and next to a robot with a mechanical arm. The height of the robotic arm is adjusted to be at the same level as the patient's shoulders. The patient is instructed to relax naturally and look straight at the computer screen in front of them. The affected forearm of the patient is secured to the handle of the robotic arm. The therapist then selects upper limb games will base on the patient's preferences and recommendations. Before entering the game interface, the therapist adjusts parameters such as gravity compensation value, training mode (active, assisted, or passive), training time, and music. In the note grabbing game, the patient is required to touch notes from different directions using the affected upper limb and count the number of touches. In the fishing game, the robot arm simulates a real fishing scene and places fish hooks on small fish of different colors that constantly change positions. The small fish are then placed in corresponding color fish frames on both sides. In the table tennis game, the patient can compete online with patients from different locations, imitate real movements, hit the ball back from the opponent, and the competition is recorded. For upper limb joint activity training, the patient can initially passively complete the movements following the system's instructions (this step can be skipped if already proficient). Once proficient, the patient can select a training mode will base on the condition of their upper limbs. The joints will train include 8 movements of the shoulder joint (forward flexion, posterior extension, abduction, adduction, external rotation, internal rotation, horizontal abduction, horizontal adduction), as well as elbow flexion and extension, and forearm pronation and supination.

**6.3 Intervention plan for BWS-TCY+CRT group**

In the CRT+BWS-TCY group, patients undergo 30 minutes of CRT treatment and 30 minutes of BWS-TCY training daily. During BWS-TCY training, patients will watch videos and learned TCY movements with the assistance of professionally trained therapists. They will be required to skillfully apply these movements. The exoskeleton rocker of the rehabilitation robot, which can customize the TCY movement trajectory, helped the patients with restricted limbs to complete TCY movements. The training process will involve the following steps: 1) Sitting upright, relaxing the body naturally, keeping the head upright, and maintaining direct eye contact with the person on the screen in front. This top-down conscious guidance facilitated overall body relaxation. 2) The affected forearm will be fixed on the handle, with the hand in an extended position. 3)The patient will follow the pre-saved TCY motion trajectory, allowing the robot's mechanical arm to assist in carrying out the TCY action. This will involve moving the shoulders, elbows, and wrists together to draw a circle clockwise from top to bottom and from inside to outside. Studies have demonstrated that as the weight support ratio increases, the degree of muscle activation gradually decreases^[38]^. Therefore, the weight support ratio was set at 40% at the beginning of the 12-week intervention program. The program followed the principle of starting from easy to difficult and repeating intensively. It was divided into 5 different weight support stages: Weeks 1-3: 40%; Weeks 4-7: 30%; Weeks 8-10: 20%; Weeks 11-12: 0%.

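### The BWS-TCY weight-support schedule announces five stages but lists four, and its 12 weeks conflict with the 4-week duration and the 4-week per-protocol rule

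*Protocol*

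**What the plan says.** Protocol section 6.3 describes the progression of weight support in the BWS-TCY+CRT arm. It gives a starting level and a programme length: "the weight support ratio was set at 40% at the beginning of the 12-week intervention program". It then announces the number of stages and lists them: "It was divided into 5 different weight support stages: Weeks 1-3: 40%; Weeks 4-7: 30%; Weeks 8-10: 20%; Weeks 11-12: 0" (the final figure is a percentage, 0%).

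On duration, section 6 agrees with this schedule: "The rehabilitation intervention will last for 12 weeks, with sessions of 60 minutes per day, 5 days per week". The Project summary, Expected outcomes of the study and Duration of the project sections also give 12 weeks of intervention. The Study design section says otherwise: "The rehabilitation interventions will last 4 weeks".

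Section 8 (Statistical method) places in the per-protocol analysis those randomised participants who do not stop treatment early and who complete 4 weeks of treatment.

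**The concern.** Graded weight support is the named feature of the experimental treatment, and section 6.3 itself links the support ratio to the degree of muscle activation. The level in a given week is therefore part of what is being tested. Two things do not fit.

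First, the count and the list disagree within one sentence. A reader cannot tell whether the author miscounted or dropped a stage.

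Second, the schedule needs 12 weeks, while one section ends treatment at 4 weeks and another treats 4 weeks as completion. At stake is what the experimental arm receives and what the per-protocol estimate describes: the effect of the whole progression, or of its first third.

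**Working it through.** **Stage count.** Inputs are from section 6.3.

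| Listed stage | Weeks | Length | Level | Drop from previous level |
|---|---|---|---|---|
| 1 | 1 to 3 | 3 | 40% | – |
| 2 | 4 to 7 | 4 | 30% | 10 points |
| 3 | 8 to 10 | 3 | 20% | 10 points |
| 4 | 11 to 12 | 2 | 0% | 20 points |

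- Announced: 5. Listed: 4 stages with 4 distinct levels. The announced figure is not reproduced.
- Total length: 3 + 4 + 3 + 2 = 12 weeks. Each week from 1 to 12 is assigned exactly once, so a fifth stage would require changing the listed weeks.
- The last drop (20 points) is twice each earlier one (10 points). That is compatible with an omitted stage but does not prove one; a miscount explains the text equally well.
- No other section repeats the schedule or supplies a fifth stage. Section 5 describes only what the device can adjust.

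**Schedule against duration.** Inputs are the listed weeks, the 4 weeks in the Study design section, and 5 days per week from section 6.

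- Delivered in a 4-week course: weeks 1 to 3 at 40% and week 4 at 30%.
- Not delivered: 3 weeks at 30% (weeks 5 to 7), 3 weeks at 20% and 2 weeks at 0%, so 3 + 3 + 2 = 8 of 12 weeks.
- Levels never reached: 20% and 0%, which is 2 of 4.
- Training days: 4 × 5 = 20, against 12 × 5 = 60.

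**Schedule against the per-protocol rule.** Section 8 has two conditions: no early stop, and 4 completed weeks.

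- If early is judged against 4 weeks, a participant with three weeks at 40% and one week at 30% is a completer, and the 20% and 0% levels are not required.
- If early is judged against 12 weeks, the first condition already demands the full course and the 4-week condition adds nothing.

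The protocol does not say which duration the first condition refers to, so the rule inherits the conflict.

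**The case against.** The strongest reply is that the list can be followed as it stands. It gives each of the 12 weeks one support level, and it is the only schedule in the document. The number five supplies no rival percentage or week range, so therapists are not offered two progressions. On this view the count is a slip in one word, with no bearing on sample size, alpha or power. This stands, and it is why the stage count alone is a minor matter.

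It can also be said that the 4-week against 12-week conflict is a separate defect that would exist whatever the number of stages. That is true as a matter of origin. It still belongs here, because the weight-support schedule is where the conflict has a concrete result: half of the listed levels depend on which duration applies. Correcting the count without settling the duration would leave the schedule unresolved.

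A third reply is that 4 weeks in section 8 may be meant as a minimum exposure within a 12-week course, or that an analysis plan not available here defines the set in full. Either is possible. The protocol's wording does not call it a minimum, however, and the Study design section gives the same 4 weeks as the whole intervention.

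**Conclusion.** The point holds as an internal contradiction. One sentence of section 6.3 announces five stages and lists four that already fill weeks 1 to 12, and nothing elsewhere resolves it. The 12-week schedule also contradicts the 4 weeks in the Study design section. Under that duration two of the four levels would not be reached, and under the 4-week condition in section 8 they would not be required. These figures take the listed weeks and levels at face value.

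Some stronger conclusions are tempting but not supported:

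- A reader might infer that the progression is undefined, that adherence cannot be judged, or that the treatment cannot be reproduced. The list assigns one level to every week, so it can be followed and adherence can be checked against it. The doubt is whether it is the list that was intended.
- A reader might infer that a stage is certainly missing. The unequal last step is suggestive only.
- A reader might infer a tolerance problem at the final step. The protocol gives no data on tolerance of the support levels, so that would be clinical opinion and not a contradiction in the document.
- A reader might take the adjustable gravity compensation in section 5 as a further conflict. It describes a device capability and states no schedule.

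**What to change.** The sponsor, with whoever is clinically responsible for the intervention, should make three linked changes:

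1. In section 6.3, reconcile the announced number of stages with the listed levels and weeks.
2. Reconcile that schedule with the duration in the Study design section, so that every section giving an intervention length agrees.
3. In section 8, align the per-protocol completion condition with the reconciled duration, and state the duration against which an early stop is judged.

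This review does not say which count, schedule or duration is correct.

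The cost is a short protocol amendment and a note to the treating therapists. If participants have already been treated, the amendment should also record the schedule that was actually delivered. The stage-count correction by itself leaves the sample size calculation untouched.
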